## Abstract

**Background:**

Rates of chronic disease are escalating around the world. To date health service evaluations have focused on interventions for single chronic diseases. However, evaluations of the effectiveness of new intervention strategies that target single chronic diseases as well as multimorbidity are required, particularly in areas outside major metropolitan centres where access to services, such as specialist care, is difficult and where the retention and recruitment of health professionals affects service provision.

**Methods:**

This study is a longitudinal investigation with a baseline and three follow-up assessments comparing the health and health costs of people with chronic disease before and after intervention at a chronic disease clinic, in regional Australia. The clinic is led by students under the supervision of health professionals. The study will provide preliminary evidence regarding the effectiveness of the intervention, and evaluate the influence of a range of factors on the health outcomes and costs of the patients attending the clinic. Patients will be evaluated at baseline (intake to the service), and at 3-, 6-, and 12-months after intake to the service. Health will be measured using the SF-36 and health costs will be measured using government and medical record sources. The intervention involves students and health professionals from multiple professions working together to treat patients with programs that include education and exercise therapy programs for back pain, and Healthy Lifestyle programs; as well as individual consultations involving single professions.

**Discussion:**

Understanding the effect of a range of factors on the health state and health costs of people attending an interdisciplinary clinic will inform health service provision for this clinical group and will determine which factors need to be controlled for in future observational studies. Preliminary evidence regarding changes in health and health costs associated with the intervention will be a platform for future clinical trials of intervention effectiveness. The results will be of interest to teams investigating new chronic disease programs particularly for people with multimorbidity, and in areas outside major metropolitan centres.

**Trial registration:**

Australia and New Zealand Clinical Trials Registry: ACTRN12611000724976

## Background

A unique student-led interdisciplinary chronic disease health service was established in regional Australia in 2010 to address workforce shortages and spiralling rates of chronic disease in rural and regional Queensland. The service also aimed to improve local clinical placement options for allied health students. The service was established in a shopping centre with easy access using public transport.

Demographics of the people attending the service in the first year of the service (prior to commencement of the study) revealed very high rates of multimorbidity (97%) and higher rates of indigenous clients (7.1%) compared with the local community (5.9%) [1]. These demographics are relevant to the expected health outcomes of people attending the service as people with multimorbidity have worse health outcomes [2], and place a larger burden on the healthcare system than those with a single chronic disease. Additionally, indigenous Australians generally have worse health outcomes than non-indigenous Australians; including mortality and disability rates [3].

Interdisciplinary care has been promoted as a solution to maintain or improve the quality of healthcare, particularly in regional and rural areas [4-6] where health service disparity, healthcare access, and a worse burden of chronic diseases may place people living in these areas at a disadvantage in comparison to metropolitan areas [7]. Despite this, there are few high quality studies that evaluate the effectiveness of interdisciplinary care for chronic disease or primary care [8], even in metropolitan areas.

This paper describes the study protocol of a longitudinal evaluation of a unique interdisciplinary health service established in a regional Australian city to address chronic disease. The study will estimate the health outcomes and associated health costs of people attending the service.

## Methods

### Setting and services

The regional interdisciplinary chronic disease health service is located in a regional city (Rockhampton) approximately 700 kilometres from the state’s capital. Services are provided to people with chronic diseases in the regional city and surrounding rural and remote areas (providing services to more than 100,000 residents). Referral to the interdisciplinary clinic can arise from three sources: self referral, referral from the local hospital or referral from a general medical practitioner; although the majority (90%) are referred by their general practitioner [1]. Services are delivered by an interdisciplinary team of nurses and allied health professionals, including podiatrists, occupational therapists, exercise physiologists, a social worker, a speech pathologist, a dietician, a physiotherapist, a pharmacist and an indigenous health worker. Qualified professional supervisors in allied health disciplines supervise up to four students each who provide a range of services to clients with a wide range of chronic diseases that include hypertension, osteoarthritis, high cholesterol, diabetes, and chronic back pain. The process for obtaining services is shown in Figure 1.

**Figure 1 F1:**
[figure not shown]
The process for receiving services at the interdisciplinary clinic.

### Study design

A longitudinal cohort study focusing on the health outcomes and costs of patients with chronic diseases attending the service will be implemented. Patients will be evaluated at baseline (intake to the service), and at 3-, 6-, and 12-months after intake to the service. The 3- and 6-month follow-ups were included to evaluate short-term outcomes after commencement of the intervention. The 12-month follow-up was included to evaluate intermediate outcomes to pick up a potential delay in the positive impact of intervention on some dimensions of health. This study has been prospectively registered with the Australian and New Zealand Clinical Trials Registry (ACTRN12611000724976).

### Study objectives

#### ***Aims***

1. To examine the effectiveness of the service up to 12-months post-intake in improving a range of health outcomes (including length of stay in hospital, number of admissions, health state, preference based health state, and health-related costs).

2. To examine the effect of a range of factors including comorbidities, sociodemographic factors, and type of intervention received, on the health state, preference-based health state, length of stay in hospital, number of admissions, and health-related costs of people attending the service up to 12-months post intake.

3. To determine the difference in health between clients attending the service before and after receiving intervention and the general population using Australian population normative data.

#### ***Hypotheses***

1. Health will be maintained or improve over time from intake (baseline) to 12-months after intake with a small average effect size anticipated for improvement (effect size ≤ 0.2).

2. Health outcomes will be moderately to strongly and negatively associated with the number of chronic diseases (effect size ≥ 0.5).

3. Days in hospital and inpatient admission costs will decrease after intake to the service compared with before intake to the service.

4. The health of clients attending the service will be worse than the general population using Australian population normative data at all times (effect size ≥ 0.2).

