### Sample size and power

A minimum sample size of 130 participants is required to examine the change over time from baseline to 12-months post-intake of the SF-36; using a one-group longitudinal design, a power of 80% with a two-sided type 1 error of 5% to detect a difference of at least 5 points in the social functioning scale of the SF-36 using a t-test [33]. Three to five points of change in SF-36 scores has been reported as the minimally clinically important difference [33,34] and is equivalent to a small effect size for those with chronic diseases [34]. A small effect size is anticipated for changes in health over 12-months based on the small to large effect sizes found in treatment effectiveness studies using the SF-36 in related chronic disease studies over similar times [7,12,34,35] and the high percentage of clients with multiple chronic diseases attending the service prior to the study commencement, for whom moderate to large effect sizes are unlikely. The sample size calculation was based on the social functioning scale of the SF-36 as this outcome would likely show the smallest difference and therefore need the largest sample size. Therefore, provided the study sample size exceeds 130 participants, this investigation should have greater than 80% power for all outcomes.

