### Data analysis

Descriptive statistics and exploratory plots (boxplots or histograms) will be used to describe the outcome variables (e.g., health state, preference based measure of health, hospital utilisation, and costs) and potential predictors (e.g., age, employment status).

SF-36 scale raw scores will be transformed to a 0 to 100 scale. Results will be analysed using the 8 scales and the summary scores where appropriate. Scatterplots of the relationship between variables will be examined to check for linearity or potentially non-linear associations. Mean SF-36 scores will be plotted over time by demographic and disease subgroups to visually examine chronic disease progression. Regression models will be used to examine the effect of time and predictors on post-intake SF-36 scores. The scores will be modelled at 3- to 12-months with the baseline score as a predictor in order to: i) analyse the change from baseline; ii) help control for regression to the mean [36]. Mixed models will be used with subject-specific intercepts to model the dependence in results over time from the same subject. The lasso technique will be used to choose the best set of predictor variables from an initially large set of potentially important variables [37]. The residual distribution of the best model will be examined to check that it is approximately normally distributed with no large outliers. The count outcome variables (i.e., cost, days in hospital, and number of hospitalisations) will be analysed using the model described above but assuming a Poisson distribution.

The predictors to be examined in all of the models will be: BMI and waist measurement, disease burden, number and type of comorbidities, self-reported health perception, age, gender, indigenous status, country of birth, language (other than English), marital status, home ownership, highest level of education, occupation and employment status, length and type of intervention; and baseline psychological distress or wellbeing, functional and structural social support, and physical function. Health (measured using the SF-36) and the preference based measure of health will be examined as predictors for count outcomes.

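### Hypothesis 1 predicts that health is maintained or improves, but the study is sized for a test of difference and nothing defines 'maintained'

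*Protocol article*

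**What the plan says.** Hypothesis 1 (protocol article, Hypotheses) is: "Health will be maintained or improve over time from intake (baseline) to 12-months after intake with a small average effect size anticipated for improvement". The effect size attached to it, at most 0.2, concerns improvement only. No figure says how much decline would still count as maintained.

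The Sample size and power section sets the size: "A minimum sample size of 130 participants is required to examine the change over time from baseline to 12-months post-intake of the SF-36". The basis is "a power of 80% with a two-sided type 1 error of 5% to detect a difference of at least 5 points" on the social functioning scale, by t-test. The same section supplies a yardstick: "Three to five points of change in SF-36 scores has been reported as the minimally clinically important difference".

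The Data analysis section plans mixed regression models with subject-specific intercepts: "The scores will be modelled at 3- to 12-months with the baseline score as a predictor". It gives no margin, no equivalence or non-inferiority comparison, and no confidence-limit rule.

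Aim 1 speaks only of improving outcomes. The idea of maintenance enters with Hypothesis 1.

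**The concern.** The hypothesis and the test have different forms. A two-sided test asks whether mean change differs from zero. Failing to show a difference does not show that there is none, or that any decline is small. Improvement fits Hypothesis 1, and so, on its face, does no detected change, so only a demonstrated decline contradicts it. The fewer people analysed at 12 months, the harder a real decline is to demonstrate, so imprecision works in favour of the service.

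Decline is a realistic outcome here. The Discussion itself raises conditions that tend to worsen whatever treatment is given, with reference to the many multimorbid participants expected. It also says that the results will inform other health services considering similar models. A conclusion that health was maintained, drawn from a non-significant result, could therefore carry weight that the data do not support.

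**Working it through.** **Inputs from the protocol article:** n = 130; 80% power; two-sided 5%; 5-point difference on SF-36 social functioning; one-group t-test; important difference of 3 to 5 points.

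**Assumptions, not in the document:** the SD of the 12-month change, and 91 analysed after a 30% loss (0.70 × 130 = 91).

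**1. The plan's own figure.** The paired-test formula is n = [SD × (1.960 + 0.842) / 5]². No SD is given, so 130 cannot be reproduced independently; it can only be solved backwards:

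- Normal approximation: SD = 5 × √130 / 2.802 = 20.35.
- Noncentral t: SD = 20.2.

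An SD of 20 gives n = 128, so the stated size is consistent with an SD of change of about 20. I use 20.2 and show a range of 15 to 30.

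**2. Chance that a true decline is not significantly worse.** For a true decline d, the noncentrality is d × √n / SD. The miss probability is the chance that the noncentral t falls short of the two-sided 5% critical value in the direction of decline. For d = 3 and n = 130, the noncentrality is 3 × 11.40 / 20.2 = 1.69, against a critical value of 1.98.

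| True mean decline | n = 130, SD 20.2 | n = 130, SD 15 to 30 | n = 91, SD 20.2 |
|---|---|---|---|
| 3 points | 61% | 38% to 80% | 71% |
| 4 points | 39% | 15% to 67% | 54% |
| 5 points | 20% | 4% to 53% | 35% |

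At n = 130 and SD 20.2 the miss probability is 50% at a decline of 3.5 points. That is also the half-width of the 95% confidence interval (1.98 × 20.2 / √130 = 3.5).

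**3. What a confidence-limit rule would need.** Require the lower 95% limit of mean change to lie above −m (one-sided 2.5%), with true change 0 and SD 20.2:

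| Margin m | Power at n = 130 | n for 80% power |
|---|---|---|
| 5 points | 80% | 131 |
| 4 points | 61% | 203 |
| 3 points | 39% | 358 |

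With 91 analysed, a 5-point margin has about 65% power (100% − 35%, by symmetry with the table in step 2). These powers are for the lower limit clearing −m. They include the 2.5% of studies in which it also clears 0 by chance.

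**4. Why a margin alone is not enough.** An interval can lie wholly between −5 and 0 once its half-width is below 2.5 points. At SD 20.2 that needs roughly (1.96 × 20.2 / 2.5)² ≈ 251 analysed. The stated 130 is a minimum, so a larger study could show a significant decline that still clears a −5 limit. The rule must exclude that case.

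All these figures are for the paired t-test used for sizing. The planned mixed model may be more or less precise.

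**The case against.** The strongest reply is that the protocol contains no rule by which a null result confirms Hypothesis 1. A reader might infer that a non-significant result counts as support, but no section says so. That stands: the defensible statement is that nothing prevents this reading.

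A reader might also infer that an important decline would usually be missed, or that the hypothesis is close to unfalsifiable. The figures do not support either. Under the back-solved SD, a miss is more likely than not only below about 3.5 points. At the 5-point difference on which the study is sized, a decline is detected 80% of the time, and a significant decline would refute the hypothesis. With an SD of 15, even a 3-point decline is missed in only 38% of studies.

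It is also fair to say that the t-test is the sizing test and not the planned analysis, that 130 is a minimum, that the study offers preliminary evidence, and that a margin is often set in a statistical analysis plan. But the mixed model as described has no criterion for maintenance either. The mismatch also lies within this document, which states a no-decline hypothesis and sizes the study for a difference.

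Finally, social functioning was chosen for sizing because it was expected to show the smallest difference, so it is not obviously the best single test of health. That is a reason to report the other scales in the same way; it does not justify leaving the criterion undefined.

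**Conclusion.** The point holds as a mismatch between hypothesis and test. Maintenance is predicted, the study is sized to detect a difference, and no criterion says when maintenance has been shown.

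The cost is moderate and depends on the size of the decline. At the lower end of the plan's important range the sizing test would more often miss a decline than detect it; at the upper end it would miss about one in five. Loss to follow-up moves every figure in the direction that favours the hypothesis. The percentages rest on an SD of change that the protocol does not give, on an assumed 30% loss for the n = 91 figures, and on the paired t-test. The logical gap does not depend on any of these.

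**What to change.** State that *maintained* will not be concluded from a non-significant result. Judge Hypothesis 1 from the 95% confidence interval for mean 12-month change, estimated from the planned model, on social functioning as the scale on which the study is sized. Report the other scales in the same way. Use four labels:

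- *Improved*: lower limit above 0.
- *Maintained*: lower limit above the negative of a margin stated in advance, and the interval includes 0.
- *Declined*: upper limit below 0.
- *Inconclusive*: anything else.

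Choose the margin from the plan's own 3–5 point range and justify it. A 5-point margin fits the stated size but does not exclude a decline of 3 or 4 points. A 3-point margin is stricter but has low power at 130. State the power alongside the choice: with true change 0, about 80% (5-point margin) and 39% (3-point margin) with 130 analysed, and about 65% for the 5-point margin with 91 analysed. Give the assumed SD of change as well.

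The cost is a margin, a named deciding scale and time point, and a reporting rule. No new data are needed, and no larger sample if a 5-point margin is justified and 130 are analysed. The downside is that a null result with a wide interval must be reported as inconclusive.

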### Participants and selection criteria

All clients who attended the service will be eligible to participate. The following are inclusion criteria: presence of at least one chronic disease; aged 18 or older; and attendance at their first intake appointment. In addition, clients will be required to attend a minimum of one intervention session at the service for follow-up data to be included in analyses of clinic effectiveness over time. The following are exclusion criteria: a severe communication disability or behavioural disorder that would compromise the ability to participate in the intervention program or complete the questionnaires; a cognitive deficit that impairs the ability to read and write; and known pregnancy or up to 6-months postpartum that would influence body mass index (BMI), waist measurements, and possibly other outcomes. All participants receive individually tailored care prescribed by the service.

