### Health outcomes

Health will be measured using the Australian SF-36 (Version 1). The SF-36 is a 36-item generic measure of health with eight scales including physical functioning, role limitations, bodily pain, social functioning, general mental health, role limitations, vitality, and general health perceptions [9]. Two summary scores are obtained from these scales: a physical components summary and mental components summary. Extensive psychometric testing has occurred using people with a wide range of chronic diseases or single chronic diseases [10-13]. A review of studies has demonstrated that the SF-36 is superior in terms of sensitivity to change and responsiveness compared to other measures of health [9]. In addition, the SF-36 has been shown to discriminate between types and severities of chronic diseases and to distinguish between people with a chronic medical condition only, from those with a chronic medical condition plus a psychiatric disorder [14]. A preference-based measure of health will be derived from the SF-36 to produce a summary health score (multi-attribute utility score) for individuals at each time point.

Hospital utilisation will be measured using the number of days spent in hospital and number of hospital admissions during the one-year follow-up as indicators for intervention effectiveness. This will be accessed from hospital records for each participant.

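### The effectiveness analyses keep only clients who attend a session after intake, although baseline and follow-up start at intake; this may bias the estimates in a direction the plan cannot show

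*Protocol article*

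**What the plan says.** All places are in the Protocol article.

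- **Entry.** Under Participants and selection criteria, a client needs a chronic disease and must be "aged 18 or older; and attendance at their first intake appointment". No session is needed to enrol.
- **Clock.** Study design: "Patients will be evaluated at baseline (intake to the service), and at 3-, 6-, and 12-months after intake to the service".
- **Analysis set.** Participants and selection criteria adds: "clients will be required to attend a minimum of one intervention session at the service for follow-up data to be included in analyses". The rest of that sentence limits the rule to the effectiveness analyses. No deadline is set for the session.
- **Aim.** Aim 1 is "To examine the effectiveness of the service up to 12-months post-intake in improving a range of health outcomes", and its list of outcomes includes length of stay, admissions and costs as well as health state.
- **Hospital hypothesis.** Hypothesis 3: "Days in hospital and inpatient admission costs will decrease after intake to the service compared with before intake to the service".
- **Data sources.** For hospital use, Health outcomes says "This will be accessed from hospital records for each participant". Healthcare costs takes Medicare and pharmaceutical benefits data for 12 months either side of intake. Study measures provides for questionnaires to be posted to people who cannot come in for a follow-up assessment.
- **Missing data.** Data analysis describes inverse probability weighting for subjects who miss a whole visit, from a model with time and baseline demographic and comorbidity factors.

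**The concern.** Time zero is intake, but whether a client counts towards effectiveness depends on something that happens later. If attending a first session is related to how a client fares after intake, the retained group is a selected one, and its average change differs from that of everyone taken in.

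Hospital use shows the mechanism most clearly. A client who is admitted soon after intake and never starts is dropped, and the post-intake bed days and costs go too. In a one-group before/after design no comparison arm would share the selection and reveal it. The anticipated effect is small (Hypothesis 1 gives an effect size of at most 0.2), so even a modest shift matters in relation to it.

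**Working it through.** **1. Does the rule reach hospital and cost outcomes?** Aim 1 lists them among the outcomes on which effectiveness is judged, and Health outcomes calls hospital use an indicator of intervention effectiveness. On a plain reading, it does.

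**2. Who is removed?** Only clients who never attend a session. As there is no deadline, a client who is admitted or worsens after intake and later attends once stays in, with those hospital days counted.

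**3. Does the weighting restore them?** It is described for missed visits, whereas these clients are excluded by rule. Even if they were treated as missing, a model limited to time and baseline factors could not correct for selection on events after intake.

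**4. Size of the bias in mean change.** Let q be the share of enrolled clients with no session, A the mean change in attenders, N the mean change in non-attenders, and D = A − N.

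- Mean change in all clients = (1 − q)A + qN
- Bias of the restricted estimate = A − [(1 − q)A + qN] = q × D

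The document gives neither q nor D. Assumed values for SF-36:

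| q | D = −5 | D = 0 | D = +5 |
|---|---|---|---|
| 10% | −0.5 | 0 | +0.5 |
| 20% | −1.0 | 0 | +1.0 |
| 25% | −1.25 | 0 | +1.25 |

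Over a wider range, q from 5% to 30% and D from −10 to +10, the bias runs from −3.0 to +3.0 points (0.30 × 10). Against the 5-point difference in Sample size and power, 0.5 to 1.25 points is 10% to 25%.

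**5. Effect on a simple test of no change.** The plan's minimum of 130 needs an SD of change, which is not given. Back-solving a one-sample t-test (two-sided 5%, power 80%, 5 points) gives an SD of about 20.2; the normal approximation gives 5 × √130 / (1.960 + 0.842) ≈ 20.3. So 130 is consistent with such an SD but cannot be verified from the stated inputs. With N = 130, SD 20.2 and a true overall change of zero, the test rejects 5.9% of the time at a bias of 0.5 point, 8.7% at 1 point and 20.2% at 2 points.

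**6. Check on the sign.** A simulation used zero true change, SD 20.2, an assumed correlation of 0.5 between early and 12-month change, and an assumed log-odds slope for attendance of 0.5 per SD of early change. Mean change in the retained clients was:

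| Who tends not to attend | q = 10% | q = 20% |
|---|---|---|
| Early deteriorators | +0.50 | +1.00 |
| Unrelated to change | about 0 | about 0 |
| Early improvers | −0.48 | −0.97 |

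**7. Hospital days and costs.** The same identity applies, with D as the difference in before/after change in days or costs. The document gives nothing from which to set q or D, so no figure is offered.

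**The case against.** **Change among treated clients is a proper target.** The abstract describes a comparison before and after intervention, and Aim 3 uses similar terms. Clients with no session say nothing about the effect of sessions, and there is no randomised comparison to protect. This stands, and the restricted analysis should be kept. It does not answer Aim 1 and Hypothesis 3 in full, because both are anchored at intake.

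**The direction is not known.** A reader might infer that the rule removes early deteriorators and so favours the service. The document does not support that. It gives no number of non-attenders, no reasons and no information on their course. Clients with milder disease, or who improve early, may also not return, and that would bias against the service. Nor are all clients who are admitted or worsen before a first session removed; those who attend later remain. This objection stands in full.

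**The size is assumed and modest.** Also true: 0.5 to 1.25 points lies below the 3 to 5 points that the plan cites as minimally important.

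**An article condenses.** A supplementary all-enrolled analysis may be set out in a fuller document, and its absence here is not the point. The point is the rule that the article states.

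**The remedy is partial.** Clients who die have no later SF-36, and those who worsen may not return a posted form. The gain is mainly in the record-based outcomes.

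**Conclusion.** The point holds in limited form. The effectiveness set is defined by attendance after baseline while every clock starts at intake, and the planned weighting does not address that selection. The estimates may be biased. For hospital use a favourable bias is plausible, because a client who is admitted and never starts takes post-intake days and costs out of the analysis; it is not shown. For SF-36 the bias is q × D, of either sign: ±0.5 to ±1.25 points if 10% to 25% never attend and the groups differ by 5 points. Both inputs are assumptions, and the false-rejection rates also rest on a back-solved SD. This is an inexpensive improvement to the plan, and it does not make the restricted analysis invalid.

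**What to change.** 1. Keep the at-least-one-session analysis and label it as change among clients who received intervention.
2. Beside it, run the same analysis in all consenting clients with an intake appointment: at minimum for hospital days, admissions and costs, which need no session attendance, and with any SF-36 returned by clients who had no session.
3. Report how many clients the rule excludes and their baseline SF-36.

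The cost is one further run on records that the plan already describes obtaining. The downside is that the all-intake estimate is diluted by clients who had no sessions, so the two results answer different questions and should be read together.
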